#### *6.2.3 Missing data*

Missing data will be reported in the relevant publications. We do not expect any missing data for the primary outcome (except for those discharged within the 24 hours) or the key secondary outcomes. Patients discharged within 24 hours or who died within 24 hours, will be included in the ITT analysis with the amounts they received until discharge/death. We do not expect missing data on mortality or adverse events. Multiple imputation using known risk factors for outcomes in sepsis will be used to impute values for patients with missing data if missing data is substantial (> 10%).

#### *6.2.4 Statistical stopping criteria*

Since the primary outcome is not mortality, there will be no formal stopping criteria for efficacy. There will be no predefined stopping criteria for futility since enrollment of the full cohort might allow for detection of differences in other outcomes even if the primary outcome is negative.

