### 3. TRIAL DESIGN

#### 3.1 Overview

This is an investigator-initiated, multicenter, randomized, parallel-group, open-labeled, feasibility trial investigating volumes of fluid within 24 hours in 124 patients with sepsis allocated to two different IV fluid regimens enrolled at three emergency departments in Central Region Denmark. The objective is to assess the feasibility of a trial comparing two approaches to intravenous fluid resuscitation of sepsis; a restrictive approach using four criteria vs. standard care. The hypothesis is that the restrictive approach is feasible and will result in less IV fluid given. The primary outcome is total intravenous fluid volume within 24 hours and key secondary outcomes include protocol violations, total fluids (intravenous and oral) within 24 hours, progression to septic shock, and SAEs/SUSARs.

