#### **5.2 Secondary outcomes**

##### *5.2.1 Definitions*

The secondary outcomes will be

- Feasibility measures:
  - Number of patients with major protocol violations,

- Number of patients screened positive (ie.with all inclusion criteria fulfilled and no exclusion criteria fulfilled) vs randomized
- Time from admission to inclusion
- Number of patients lost to follow up in terms of 24-hour fluids (e.g. due to discharge within 24 hours)
- Accumulated serious adverse reactions and events (SAEs + SARs+ SUSARs) within 7 days in-hospital
- Total fluids (oral and intravenous) at 24 hours

We will also report in-hospital mortality and 30- and 90-day mortality (possible outcomes for the final large scale trial), in-hospital length of stay (LOS), mechanical ventilation within 7 days of admission (yes/no), vasopressor use within 7 days of admission (yes/no), and development or worsening of acute kidney failure according to the KDIGO3-criteria within 7 days of admission (also an SAE, see above) .

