#### *5.2.2 Elaboration on secondary outcomes*

The study is a feasibility trial only powered to answer the primary aim. However, we regard the above mentioned as important feasibility measures. The trial will include additional outcomes focused on hemodynamics, organ failure, and long-term outcomes in order to be able to power calculate for the planned large-scale trial.

Both 30-day and 90-day survival will be obtained from electronic medical records or the Danish Civil Personal Register which allows for accurate and virtually complete follow-up.

We will include 90-day survival as a measure of long-term survival. 90 days were chosen since it is unlikely that mortality later than that will be directly linked to the sepsis event or the trial interventions.

A vasopressor will be defined as any continuous infusion of noradrenaline, dopamine, dobutamine, terlipressin, vasopressin, phenylephrine, and/or adrenaline. Receiving vasopressors for a total of at least 3 hours on a given day is defined as receiving vasopressors for that day. Invasive ventilation is defined as mechanical ventilation through an endotracheal or tracheostomy tube, not only used for surgery for a total of at least 3 hours on a given day.

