## **6. SAMPLE SIZE CALCULATION AND STATISTICAL ANALYSIS PLAN**

### **6.1 Sample size calculation**

The trial will be powered to the primary outcome of 24-hour total intravenous fluids. Sample size calculation is based on unpublished data from an observational study conducted in three of the hospitals in Central Denmark Region. The study found that sepsis patients received a mean of 3762 ml (SD 1839) intravenous and oral fluid in 24 hours. Looking at only patients with sepsis, blood cultures drawn and intravenous antibiotics, patients received 2670 ml intravenous fluids (SD 1695). We conservatively estimate that the total amount of IV fluid in the control group will be approximately 2650 ml (standard deviation 1.7 L). We consider a mean difference of 1 L to be clinically meaningful and therefore estimate 1650 ml (standard deviation 1.7 L) in the intervention group. Based on these estimates, an alpha of 5%, a power of 90%, and a two-sample t-test, a sample size of 124 patients is required; 62 in each treatment arm. Using the same standard deviation of 1.7 L, which is even higher than the mean in the restrictive arm, is or most conservative estimate being able to segregate the two groups.

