### **6.2 Statistical analysis plan**

#### *6.2.1 General considerations*

The statistical reporting will adhere to the CONSORT guidelines. All tests will be two-sided, a p-value < 0.05 will be considered significant, and all confidence intervals will have 95% coverage.

Patient inclusion and exclusion will be illustrated in a CONSORT flow diagram (see Appendix 7 for a draft).

We will include measures related to feasibility including the enrolled to screened ratio, time to randomization, and protocol adherence/major protocol violations. All analyses will be conducted in the intention-to-treat (ITT) population defined as all randomized participants for whom consent was obtained. We will perform the primary analyses adjusted for the stratification variable site.

The two groups will be compared in relation to baseline patient and sepsis characteristics using descriptive statistics.

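### Section 6.2.4 rests the lack of a futility rule on detecting differences in outcomes the trial is not powered for, and 6.2.1 calls any such p < 0.05 significant

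*Protocol*

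**What the plan says.** - **Threshold (6.2.1).** One rule covers everything: "All tests will be two-sided, a p-value < 0.05 will be considered significant, and all confidence intervals will have 95% coverage". Section 6.2.2 then applies between-arm linear regression to other continuous variables and site-adjusted logistic regression to binary outcomes.
- **Futility (6.2.4).** There is no predefined futility rule, and the reason given is that "enrollment of the full cohort might allow for detection of differences in other outcomes even if the primary outcome is negative".
- **Purpose of the other outcomes (5.2.2).** "The study is a feasibility trial only powered to answer the primary aim". The additional outcomes are included so that the large trial can be sized.
- **Which outcomes (5.2.1).** The listed secondary outcomes include accumulated serious adverse events and reactions within 7 days. Then: "We will also report in-hospital mortality and 30- and 90-day mortality (possible outcomes for the final large scale trial"), followed by length of stay, mechanical ventilation, vasopressor use and KDIGO3 kidney failure. That makes seven clinical outcomes and one harm outcome.
- **Listing (3.1 and Overview).** Section 3.1 names as key secondary outcomes, besides protocol violations, "total fluids (intravenous and oral) within 24 hours, progression to septic shock, and SAEs/SUSARs". Progression to septic shock appears neither in 5.2.1 nor in the Overview. The harm outcome is SARs and SUSARs within 48 hours in the Overview, SAEs, SARs and SUSARs within 7 days in 5.2.1, and SAEs/SUSARs with no window in 3.1.

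**The concern.** Sections 5.2.2 and 6.2.4 give the non-primary outcomes different jobs. Collecting event rates to size a later trial is estimation. Detecting differences after a negative primary is inference, and 6.2.1 supplies the threshold at which such a difference would be called significant.

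The trial is open label with 124 patients. Section 5.2.1 names the mortality outcomes as candidates for the large trial. If the fluid volumes do not separate, an isolated p < 0.05 on a clinical outcome would be unreliable, but nothing in 6.2 stops it from being reported with the same status as the primary result or from steering the choice of outcome for the next trial. It also matters which outcomes belong to the set, and the three lists disagree.

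**Working it through.** **1. The plan's own figure.** Section 6.1 takes a difference of 1 L ("We consider a mean difference of 1 L to be clinically meaningful"), SD 1.7 L in each arm, and "an alpha of 5%, a power of 90%, and a two-sample t-test, a sample size of 124 patients is required; 62 in each treatment arm".

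n per arm = 2 × (1.960 + 1.282)² × (1.7/1.0)² = 60.7, so 61 by the normal approximation. The t-test solution is 61.7, so 62 per arm and 124 in total, with power 90.1%. The figure reproduces and is two-sided (a one-sided test would need 50 per arm).

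**2. Power for the outcomes on which 6.2.4 relies.** From the documents: 62 per arm; about 6% in-hospital mortality anticipated (9.3.2); background mortality 10–23% (1.1.1). Halving and doubling are illustrative choices.

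Normal approximation: power = Φ[(|p₁ − p₂| − 1.96·s₀)/s₁], where s₀ = √(2p̄(1 − p̄)/62) and s₁ = √((p₁(1 − p₁) + p₂(1 − p₂))/62).

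For 6% versus 12%: p̄ = 0.09, s₀ = 0.0514, s₁ = 0.0511; Φ[(0.06 − 0.1007)/0.0511] = Φ(−0.80) = 0.21.

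| True rates | Normal approximation | Exact enumeration, Fisher to pooled z |
|---|---|---|
| 6% vs 3% | 12% | 4–11% |
| 6% vs 12% | 21% | 13–21% |
| 10% vs 20% | 34% | 26–34% |
| 23% vs 11.5% | 39% | 31–39% |
| 6% vs 24% | 81% | 76–83% |

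From a base of 6%, mortality in the other arm would have to be about fourfold for power near 80%.

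**3. Chance of at least one p < 0.05 among eight outcomes when none truly differs.** The eight are in-hospital, 30-day and 90-day mortality, length of stay, ventilation, vasopressors, KDIGO3 kidney failure, and any serious event or reaction. It is assumed that 6.2.2 is applied to each of them and that the harm outcome is analysed as any event, yes or no.

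- Independent tests of exact 5% size: 1 − 0.95⁸ = 33.7%.
- Equally correlated two-sided z-tests of exact 5% size (simulated): 29.9%, 25.0% and 19.1% at correlation 0.3, 0.5 and 0.7.
- The planned site-adjusted logistic Wald tests, with linear regression on log length of stay, simulated at 62 per arm with nested mortality outcomes and latent correlation 0 to 0.5 (4,000 runs each):

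| Assumed event rates | At least one p < 0.05 |
|---|---|
| Low (3–12%) | 12–14% |
| Middle (5–16%) | 17–19% |
| High (15–25%) | 26–29% |

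The low values arise because a Wald test on sparse events rarely rejects. At 6% mortality, about 7 deaths in 124, it rejects about 1% of the time. The supportable range is therefore about 12–34%. Apart from 6% in-hospital mortality, the event rates in the simulation are assumptions, and so are all the correlations.

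**The case against.** The strongest reply is that the protocol already treats these outcomes as secondary in substance. There is one primary outcome and one hypothesis, both on intravenous volume. Section 5.2.1 separates the outcomes it will also report from the listed secondary ones. Section 5.2.2 gives them a planning role, and 5.4.3 disclaims causal inference for SARs. The step to a large trial depends on feasibility and separation of the arms (1.3, 9.1), not on a secondary p-value. Unadjusted secondary outcomes are usual in a feasibility trial, and section 12 promises a published analysis plan that could set their status.

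Most of this stands. The lack of a multiplicity adjustment is not an error here, and an exploratory label missing from the protocol would not by itself be one. What remains is what the protocol states: a significance rule for all tests, and a reason in 6.2.4 that conflicts with 5.2.2.

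A reader might infer three stronger things, none of which the documents support:

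- **That a negative trial carries a one-in-four risk of a false finding.** That value needs an assumed common correlation near 0.5 and tests of full 5% size. It is one point in the 12–34% range.
- **That the plan breaches its own 5%.** Section 6.2.1 sets a per-test level. No family-wise rate is stated.
- **That 6.2.4 promises a clinical claim after a negative primary.** It explains, in hedged terms, why there is no futility stop. It does not say how a secondary result would be interpreted. Whether such a claim would more likely be false than true depends on prior probabilities that the protocol does not give.

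**Conclusion.** The point holds as a contradiction to be reconciled, not as a flaw in the primary analysis. Section 6.2.4 relies on detection that the design largely cannot deliver: about 13–21% power for a doubling of the anticipated 6% mortality, and no more than about 34–39% for a doubling from 10% or a halving from 23%. Section 6.2.1 would give a chance result the same label as the primary result, and with no true differences at least one would occur in about 12–34% of such trials. That range assumes that all eight outcomes are tested as 6.2.2 describes, and it moves with the assumed event rates and correlations. The power figures rest on 62 per arm and the protocol's own mortality rates. The disagreement between the secondary-outcome lists is a separate inconsistency, but it leaves open which outcomes belong to the set. The matter should be corrected, because the change is small and limits what the trial may conclude.

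**What to change.** - **6.2.1:** state that 24-hour intravenous fluid volume is the only confirmatory test, at two-sided 0.05. All other outcomes are exploratory and are reported as estimates with 95% confidence intervals, without significance claims.
- **6.2.4:** replace the reason based on detecting differences with the purpose in 5.2.2, namely event rates and precision for planning the large trial.
- **3.1, Overview and 5.2.1:** make the secondary-outcome lists agree. Either add progression to septic shock to all of them or remove it from 3.1, and give the harm outcome one content and one window (48 hours or 7 days).

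If the sponsor prefers to keep significance tests on the eight outcomes, testing each at 0.05/8 = 0.00625 would hold the chance of any false positive to 1 − (1 − 0.00625)⁸ = 4.9% under independence, at a further loss of power.

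The cost is wording only, with no extra patients or data. The sponsor gives up the option of calling a nominally significant secondary outcome a finding.

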## **7. DATA COLLECTION AND MANAGEMENT**

### **7.1 Data collection process**

Enrollment and randomization will be performed by the treating team directly in the trial specific REDCap-site. The treating team will register limited data in REDCap including patient identifier (i.e., Danish Central Personal Register number), site and inclusion/exclusion criteria, and limited trial specific data in the electronic medical record to notify the enrollment of the patient in the trial. This will include study ID, timing of enrollment and allocation. A paper-CRF (A bedside REFACED Sepsis resuscitation chart) will be placed at the patient's bedside collecting data on fluid management filled out by the treating team during the 24 hours; timing of fluids administered, indication for fluid bolus, fluid type (the precise investigative

medicinal product (IMP); 1) Sodium Chloride solution 0.9% B.Braun, Sodium Chloride 9mg/ml Fresenius Kabi, Ringers) and volume and time to re-evaluation and protocol violations and reasons for these. Further data will be obtained from the electronic medical journal by the research team as described below including for example vital signs, blood tests etc.; all data will be based on measurements and assessments made by the clinical team. A trained member of the research team (either the sponsor, site investigators or employed research nurses and medical students) will be responsible for data collection and entry into the eCRF from the electronic medical journal and from the paper-CRF. Data will be entered directly into the database software from the electronic medical journal (see section 7.4). The paper-CRF and e-CRF in REDCap will both be developed and tested and validated before initiation of the trial at all sites to optimize the use and be able to uniform the data abstraction.

### *7.1.2 Variables*

All sepsis patients at the participating sites will be entered into a screening log by daily going through all adult, admitted patients who had a blood culture performed (screening criteria) and check if these patients fulfilled inclusion criteria and exclusion criteria. The screening log will be carried out by a trained member of the research team (either the sponsor, site investigators or employed research nurses and medical students). For those not randomized, a specific reason for non-inclusion/exclusion will be documented. The screening log will for all screened patients include variables for inclusion, exclusion and for some patients the logistical reasons for not including the patients. This data will be collected either before informed consent by the “legal guardian” or for patients screened and excluded without informed consent. Data collected from the electronic patient journal before consent will be passed on to the primary investigator for use in the trial, as well as legal authorities by request. Screening for patients will be performed “real-time” by the trained research team and the treating teams, but the screening log will be filled out once daily by the trained research team going through all patients admitted since the last screening log was performed. All randomized patients will be entered into the main REDCap database.

A detailed data dictionary that clearly defines all included variables in the eCRF (elaboration of 7.1.3-7.1.8) will be created prior to patient enrollment. The data dictionary will provide the name of the variable (including the code used in the database), a detailed definition of the variable, categories for categorical variables, and units and ranges for continuous variables.

The number of collected variables will be kept relatively small to limit resource use and data entry mistakes. Below is provided a brief overview of the included variables but details are reserved for the data dictionary. The following variables will be obtained on all included patients and collected from the electronic patient journal or the paper-CRF (7.1.3-7.1.8):

### 7.1.3 Pre-sepsis baseline characteristics

#### Trial related variables

Study ID

Site

Inclusion criteria

Exclusion criteria

Date and time consent for data collection is obtained

#### Patient demographics and characteristics

Name

Unique patient identifier (CPR number)

Age

Sex

Height

Weight

#### Conditions/medications prior to enrollment

##### Co-morbidities:

- Previously admitted for:
  - Heart failure + ejection fraction and/or diastolic dysfunction
  - Myocardial infarction and/or cardiac arrest
  - Stroke
- Diagnosed with:
  - Asthma or chronic obstructive pulmonary disease Y/N,
  - Chronic treatment for arterial hypertension Y/N,
  - Chronic treatment for diabetes Y/N,
  - Haematological malignancy Y/N,
  - Metastatic cancer Y/N,
  - Dementia Y/N
  - Atrial fibrillation (chronic or paroxysmal)

- Habitual s-creatinine obtained from the laboratory systems in the electronic patient journal (worst within 5-90 days prior to admission)
- Clinical frailty index

#### *7.1.4 Sepsis characteristics*

Site of infection:

Pulmonary

Abdominal

Urinary tract

Soft tissue

Other/unknown

#### *7.1.5 Variables obtained at randomization (the closest measured around time for randomization):*

Values for SOFA-score at admission 

Results of blood samples (standard lab. Values + arterial/venous blood gas)

- Lowest values: haemoglobin, platelets, eGFR,
- Highest values: lactate, kreatinin, bilirubin, C-reactive protein, leukocytes (white blood count),

Vital parameters

- Highest heart rate, respiratory rate,
- Lowest values of mean arterial blood pressure
- Highest values of arterial or venous lactate concentration or from a blood sample

Antibiotics: Type, timing and dosage and administration form

Volume of resuscitation fluids (crystalloids, colloids and blood products in ml) until randomization

Other fluids including blood products, nutrition, fluid with medication

#### *7.1.6 Variables obtained at 6-, 12- and 24 hours after randomization:*

Hourly volumes of resuscitation fluid with specification of indication for each fluid bolus

Other fluids including blood products, nutrition, fluid with medication

Highest creatinine within 24 hours to evaluate KDIGO-criteria

Only 24hours: To evaluate worst SOFA-score within 24 hours:

Results of blood samples (standard lab. Values + arterial/venous blood gas)

- Lowest values: platelets, PaO2 (and FiO2)
- Highest values: lactate, bilirubin,

Use of renal replacement therapy Y/N

Protocol violations

Non-invasive ventilation Y/N

On mechanical invasive ventilation or vasopressor Y/N

Status: dead, Y/N

Only 24hours: SAEs (see section 5.4.3) + SARs (see section 5.4.4)

SAEs on this day (y/n for everyone)

- Cerebral ischemic event
- Myocardial ischemic event
- Intestinal ischemic event
- Limb ischemia
- New onset of severe acute kidney injury

SARs on this day (y/n for everyone)

- General tonic-clonic seizures
- Anaphylactic reactions
- Central pontine myelinolysis
- Severe hyponatremia
- Severe hyperchloremic acidosis
- Severe metabolic alkalosis

Only 24 hours: SUSARs

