### *1.2.3 Fluid restriction; pros and cons*

Recent fluid resuscitation and use seems to be quite liberal, in accordance with SSC, used for the above-mentioned reasons (section 1.2.1). However, too liberal fluid resuscitation may potentially result in worsening of tissue edema (including lungs), challenge the heart and lengthen the duration of mechanical ventilation. Liberal fluid resuscitation may also result in increased hemodilution, which may induce use of concomitant interventions (e.g., transfusion of blood products). Intravenous fluid administration has also been suggested to cause destruction of the capillary wall, causing further tissue edema. Restrictive fluid therapy may be beneficial in reducing venous backpressure and organ edema, thereby improving function of organs such as the lungs, gut, and kidneys. On the other hand, fluid restriction may compromise peripheral and/or organ perfusion through reduced cardiac output and thereby reduced microcirculation from the arterial side.

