#### *5.4.4 Definitions of serious adverse reactions in REFACED Sepsis*

Defined serious adverse reactions (SARs) are:

- General tonic-clonic seizures: Stiffening and/or jerking movements of all 4 extremities in a patient who becomes or is unconscious after randomization
- Anaphylactic reactions defined as urticarial skin reaction AND at least one of the following observed after randomization:
  - Worsened circulation (>20% decrease in systolic blood pressure or >20% increase in vasopressor dose)
  - Increased airway resistance (>20% increase in peak pressure on the ventilator) if intubated

- Clinical stridor or bronchospasm
- Subsequent treatment with bronchodilators
- Central pontine myelinolysis seen on CT or MRI scan within the 7-day after randomization
- Hyponatremia defined as P-Na > 159 mmol/L on any plasma sample including point-of-care testing after randomization if hyponatremia is not present at randomization or worsening of a preexisting hyponatremia with an increase in P-Na of > 5mmol/L from baseline (at enrollment)
- Severe hyperchloremic acidosis defined as pH < 7.15 AND p-chloride > 115 mmol/L on any plasma sample, including point-of-care testing after randomization if hyperchloremic acidosis is not present at randomization or worsening of a preexisting hyperchloremia with an increase in p-chloride > 5 mmol/L or decrease in pH > 0.05 (AND pH < 7.15 at baseline) from baseline (at enrollment)
- Severe metabolic alkalosis defined as pH > 7.59 AND SBE > 9mmol/L on any plasma sample, including point-of-care testing after randomization if metabolic alkalosis is not present at randomization or worsening of a preexisting metabolic alkalosis with a increase in pH > 0.05 and increase in SBE > 5mmol/L from baseline (at enrollment).

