#### *7.1.7 Variables on every day until 7 days from enrollment*

On mechanical invasive ventilation or vasopressor Y/N

SAEs (see section 5.4.3 + see above)

SUSARs (see section 5.4.5)

Status: dead, Y/N

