#### List of SAEs that do NOT have to be reported to the sponsor within 24 hours of occurrence

- New ischemic events defined as:
  - Cerebral ischemia as any form of cerebral ischemia on a CT- or MRI scan
  - Acute myocardial ischemia defined as participant with acute myocardial infarction (ST-elevation myocardial infarction or non-ST elevation myocardial infarction) or unstable angina pectoris according to the criteria in the clinical setting (e.g. elevated biomarkers, ischemic signs on ECG, and clinical presentation)
  - Intestinal ischemia defined as ischemia verified with endoscopy, surgery, or CT-angiography.
  - Limb ischemia defined as clinical signs and need of vascular intervention, amputation, or initiation/increased antithrombotic treatment.
- Heart failure or cardiogenic shock or cardiac arrest/death
- New onset of severe acute kidney injury (modified KDIGO3)
- Hypervolemia/overhydration, pulmonary edema

All of the above SAEs should be reported to sponsor before final report to the authorities.

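### The daily yes/no SAE list leaves heart failure and fluid overload to unprompted reporting, and the sodium reaction is labelled as low sodium but defined as high sodium

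*Protocol*

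**What the plan says.** **SAE list.** Protocol section 7.1.6 sets a list headed "SAEs on this day (y/n for everyone". It has five items: cerebral, myocardial, intestinal and limb ischemia, ending with "New onset of severe acute kidney injury". Section 7.1.7 reuses it each day to day 7 ("SAEs (see section 5.4.3 + see above").

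Appendix 3 lists the SAEs expected in this population that need not reach the sponsor within 24 hours if judged unrelated. It contains the same five and two further groups, one beginning "Heart failure or cardiogenic shock" (with cardiac arrest and death) and the other "Hypervolemia/overhydration, pulmonary edema".

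Section 5.2.1 makes the accumulated SAEs, SARs and SUSARs within 7 days a secondary outcome. Section 1.2.3 states that "too liberal fluid resuscitation may potentially result in worsening of tissue edema (including lungs" and mentions strain on the heart.

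**Sodium reaction.** Section 5.4.4 has "Hyponatremia defined as P-Na > 159 mmol/L on any plasma sample". It then counts worsening of a pre-existing case as an increase in P-Na of more than 5 mmol/L. The variable list in section 7.1.6 shows the item as "Severe hyponatremia", with no threshold beside it.

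**The concern.** Events that are asked about by name for each patient tend to be recorded more completely than events that someone must think to report. Here the prompted SAEs are all ischemia or kidney injury. The protocol's own named harm of liberal fluids, edema including the lungs, has no prompt. Nobody is blinded (section 3.4), and the unprompted route has no 24-hour deadline when an event is judged expected and unrelated. Solicited and unsolicited events are then added into one count, which will inform a planned large-scale trial.

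The sodium item is a separate matter. A person filling in the form from its label would look for low sodium, while the definition counts high sodium. SARs are counted in the secondary outcome and listed yearly to the authorities (section 5.4.6).

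**Working it through.** The plan gives no figure on this point. The sample size of 124 is powered on fluid volume and is not affected. The check is a comparison of lists, a reading of the sodium rule, and an illustration with assumed rates.

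**1. Lists side by side**

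| Event group | Appendix 3 | Yes/no list, 7.1.6 and 7.1.7 |
|---|---|---|
| Cerebral ischemia | yes | yes |
| Myocardial ischemia | yes | yes |
| Intestinal ischemia | yes | yes |
| Limb ischemia | yes | yes |
| Severe acute kidney injury | yes | yes |
| Heart failure, cardiogenic shock, cardiac arrest, death | yes | no (death has its own field) |
| Overload, pulmonary edema | yes | no |

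Appendix 3 has 4 + 1 + 1 + 1 = 7 groups. Five are prompted and two are not.

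**2. What uneven capture can do (assumed rates; the protocol gives none)**

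Let *a* be the risk of a prompted SAE, *b* the risk of an unprompted one, and *c* the share of unprompted events that get recorded. Overlap within patients is ignored. The recorded risk ratio, restrictive (R) against standard (S), is

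(a_R + c·b_R) / (a_S + c·b_S).

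Take a_S = b_S = 10%.

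- *Case A: restriction moves 5 points from overload to ischemia/kidney injury* (a_R = 15%, b_R = 5%).
  - c = 1: 20/20 = 1.00
  - c = 0.5: 17.5/15 = 1.17
  - c = 0: 15/10 = 1.50
  - Moving 2 to 10 points instead gives 16/15 = 1.07 to 20/15 = 1.33 at c = 0.5, and 12/10 = 1.2 to 20/10 = 2.0 at c = 0.
- *Case B: restriction lowers ischemia/kidney injury by 5 points and leaves overload unchanged* (a_R = 5%, b_R = 10%).
  - c = 1: 15/20 = 0.75
  - c = 0.5: 10/15 = 0.67
  - c = 0: 5/10 = 0.50

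In case A incomplete capture makes the restrictive arm look worse than it is. In case B it makes that arm look better. Both are compatible with section 1.2.3, which says restriction may reduce perfusion but may also improve lung, gut and kidney function. The value c = 0 is only a limit, because the protocol keeps these events reportable. In case A at c = 0.5, with 62 per arm, the recorded counts are 0.175 × 62 = 10.9 against 0.15 × 62 = 9.3, a gap of about 1.6 patients where the true gap is zero.

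**3. The sodium rule read literally**

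- Threshold: above 159 mmol/L, which is high sodium.
- Worsening: a rise of more than 5 mmol/L, which is also toward high sodium.
- Label: low sodium, used three times within the rule in 5.4.4 and once in 7.1.6.

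Threshold and direction agree with each other, and the label contradicts both. Because the label also works inside the rule as the baseline condition, three misclassifications follow:

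- A patient with low baseline sodium that rises by more than 5 mmol/L toward normal is scored as worsening.
- A patient already above 159 mmol/L at randomization is scored as a new event, since low sodium was not present at baseline.
- Someone working from the label in 7.1.6 alone could record low sodium, which the definition does not count.

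**The case against.** The case against runs as follows.

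- **The events are not lost.** Section 5.4.3 has investigators classify all SAEs to day 7 and report them to the sponsor. Appendix 3 requires its listed events to reach the sponsor before the final report. The SAE entries in 7.1.6 and 7.1.7 also point to section 5.4.3. This stands: the difference is between prompted and unprompted capture, not between capture and none.
- **Fluid-related harms are prompted too.** Section 7.1.6 asks yes/no about six SARs, which section 5.4.1 takes from the product characteristics of the crystalloids. This stands in part. None of the six is overload or heart failure. Section 7.1.7 names SAEs and SUSARs for the daily list but not SARs, although section 5.4.3 promises SAR assessment for 7 days.
- **Related signals are recorded.** Ventilation, vasopressor use and death are collected. They do not identify pulmonary edema, and non-invasive ventilation is listed only for 6 to 24 hours.
- **The list is only an overview.** Section 7.1.2 leaves details to a data dictionary that is not shown. That is fair, and the final form may prompt more. But this list names its items one by one and omits two groups that the protocol's own appendix names.
- **All data come from unblinded staff.** True of prompted items as well, so lack of blinding alone does not separate the groups. The missing prompt does.

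A reader might infer that the safety comparison is tilted against the restrictive arm in a known direction. The documents do not support that. The outcome combines SAEs with SARs and SUSARs, ischemia and kidney injury are not solely harms of too little fluid, and cardiogenic shock and cardiac arrest are not solely harms of too much. A reader might also infer that the sodium SAR cannot be scored. It can: the cut-off is numeric and 7.1.6 refers to section 5.4.4.

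**Conclusion.** Two defects hold, and both should be fixed, though neither threatens the primary outcome of this feasibility trial.

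First, the yes/no list prompts five of the seven SAE groups in Appendix 3. Capture is therefore uneven across types of harm in a counted secondary outcome, and overload harms are plausibly under-counted. How much, and which arm it would favor overall, cannot be worked out from the protocol. The ratios shown rest on assumed rates and illustrate only that either direction is possible. The conclusion assumes that prompted events are recorded more completely than unprompted ones and that the final form follows the list in 7.1.6.

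Second, the sodium SAR contradicts itself. This is more than a typing slip because the wrong term is part of the scoring rule. The consequence is a risk of misclassification in either direction, with no assumption needed beyond a literal reading.

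**What to change.** - In 7.1.6 and 7.1.7, make every Appendix 3 SAE group a yes/no item for all patients in both arms, on the 24-hour form and on each daily form to day 7, using the Appendix 3 definitions. This adds heart failure/cardiogenic shock/cardiac arrest and overload/pulmonary edema.
- Report the SAE components by arm alongside the accumulated count, so that a shift between types of harm is visible.
- Reconcile the sodium label in 5.4.4 and 7.1.6 with its own threshold and worsening rule, including where the term serves as the baseline condition.
- While editing, make the daily list agree with section 5.4.3 on whether SARs are assessed to day 7.

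The main changes cost two extra yes/no fields per day and one corrected term. The events are already reportable, and the sample size is unchanged.
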